**5. TREATMENT OF SUBJECTS**

Treatments in both groups are based on CBT and exposure with response prevention (ERP) protocols for face-to-face treatment of anxiety disorders according to the Dutch multidisciplinary treatment guidelines for anxiety disorders (panic disorder with or without agoraphobia, social phobia, and generalized anxiety). CBT and ERP are the most recommended treatments for anxiety, according to these guidelines (van Balkom et al, 2013).

The protocols comprise psycho-education (explanation of the treatment rationale and the general procedures in CBT treatment), cognitive therapy (examining relation between thoughts, emotions and behavior), a combination of exposure in vivo with response prevention (ERP; exposure to feared situations combined with prevention of avoidance behaviour and challenging accompanying catastrophic expectations, followed by cognitive restructuring). Depending on the type of disorder all of these components receive more or less attention in the therapy. In case of comorbidity (ie. depression) or when the initial CBT response is insufficient, psychotropic drugs are added; including Serotonin reuptake inhibitors (SSRI's) or as a next step serotonergic Tricyclic Antidepressants. The last part of the protocol will provide information on relapse prevention (identifying and adopting techniques/strategies to prevent depressive symptoms to re-occur). In accordance with standard treatment procedures parallel treatment (such as medication and/or social skills training) is allowed in both conditions, if the practitioner deems this warranted.

### CBT as usual (CBTAU)

In the CBT-TAU condition, patients receive on average 20 45-minutes sessions of face-to-face CBT, spread out over 12-20 weeks (depending on the type of anxiety disorder).

**Blended CBT (bCBT)**

In the bCBT group, patients receive 6-10 face-to-face sessions and 6-10 internet sessions, which will be delivered over a period of 12-20 weeks. Treatment starts and ends with a face-to-face session. The online sessions are delivered through a secured web-based online treatment platform (Minddistrict; www.minddistrict.com). Patients access this platform with a personalized login. The website offers information that repeats and extends the contents of the face-to-face sessions. In addition, patients use the website to complete homework exercises, such as monitoring their activities, feelings, thoughts and behavior. The first online session focuses on working with the online platform. The therapist monitors patients’ online progress and provides weekly feedback prior to the next face-to-face session. Face-to-face sessions will be audio-recorded and checked, following the same procedures as in the CBT-TAU condition. Online sessions are recorded in the online treatment platform database. On completion of treatment, patients can still access the online treatment platform to re-read information and look up homework exercises, such as the relapse prevention plan.

The same medication regimes will be administered for both conditions throughout the study. Pharmacotherapy falls under the responsibility of a psychiatrist and is provided independently of the current study.

# Investigational product/treatment

The software platform serving the blended treatment (Minddisstrict) is not a medical device, based on the 2007/47/EG guideline of the European Parliament, The Wet Medische Hulpmiddelen (Law Medical Aids) (Date of validity 15-09-2013) and the flow chart which was developed by the Nictiz, based on the MEDDEV documentation for medical aids^[[1]](#footnote-1)^. The online part of the intervention can be seen as a digital self-help workbook. The website functions as well a secure environment in which the therapist and the patient can communicate through encoded transmission channels (https).

**Privacy and security information softwareplatform: Minddistrict (www. Minddsitrict.nl)**

**Minddistrict security policy, 08102013**

**Introduction**

This document describes the measures taken by Minddistrict to ensure proper levels of service and security.

**Standards**

Minddistrict’s security policy is based on IS027001 and NEN7510 guidelines

**Data service provider**

Intermax is the Minddistrict ISO 27001 certified data service provider. ISO27001 is the basis for the series of NEN 751x norms. Intermax provides services to several Dutch hospitals and other medical institutions.

Intermax owns and administers several [VMware](http://vmware.com/) clusters, and provides virtual machines to its customers. Intermax takes care of Internet and power connections, networking and firewalling.

Servers are located accross the Netherlands only. Minddistrict is not Patriot act liable.

The virtualization technologies provided by VMware and Intermax allow Minddistrict to scale its operations. Minddistrict procures several virtual machines from Intermax. The virtual machines are Ubuntu/Linux servers.

**Audits**

General scan and penetration tests are performed by Madison Gurkha, at least once a year

**Datacenter location protection**

Intermax datacenter has implemented high level measurements to prevent unauthorized physical access to server areas, including proximity readers, biometric access control, cameras, digital code locks and security personnel.

Only authorised Intermax staff member and authorised Minddistrict (operations) staff members have access to the server space.

Intermax keeps logs of staff entering the server spaces.

**Office location protection**

Minddistrict offices are protected with personal access cards.

**Data protection**

All user data is stored in and confined to Intermax data centers.

No user data is stored anywhere on servers in Minddistrict offices.

**Transport security**

User data is transported using SSL encryption.

Maintenance operations data is transported over a VPN connection.

**Password policy**

Users determine their own passwords.

We apply a severe regime based on 12 characters including 1 special character.

Lost password are handled via a link sent via e-mail.

Passwords are stored in the database in encrypted form, not in plain text.

Systems interface security

Third party systems are connected over a VPN connection.

**Authorisation policy**

In Minddistrict organisation only two roles have access to user data: Minddistrict application managers (2 persons) and deployment managers (1 person).

Access is controlled by NDAs and by keeping access logs.

In the application patients can only access their own data. Professionals can have one or more roles: secretary, therapist, app manager, and analyst. Therapists can see data of their clients, and data of other clients, only after warning and with logging. Managers have access to patients and therapists, but not to individual patient data. Analyst have access (read only) to all data when experting the data.

**Single Sign On**

Minddistrict customers can setup a SSO connection.

Several protocols are supported: delegated login based on encryption and SAML.

**Login session time out**

After 60 minutes a session expires.

**Mobile data storage devices**

The use of mobile data storage devices such as USB and external harddrives is limited to a minimum. When used, data is encrypted.

**Development and production**

Minddistrict operations keeps a strict separation between development, testing, staging and production environments. The production architecture looks like this and is explained in the rest of this document.

**Firewall**

On the outer perimeter of the Minddistrict infrastructure, a redundant [Fortigate](http://www.fortinet.com/products/fortigate/) hardware firewall monitors incoming and outgoing traffic. The firewall is instructed to only allow incoming HTTP and HTTPS traffic from the Internet. The firewall can be instructed to block Denial-Of-Service attacks or throttle traffic.

On the servers behind the first firewall, we use the [iptables](http://en.wikipedia.org/wiki/Iptables) software firewalls in order to monitor traffic between the Minddistrict servers.

**Application servers**

The Minddistrict infrastructure consists of multiple application servers over which the computational load is spread in order to keep response times low.

The application servers are identical servers that accept requests and return web pages. The application servers connect to the database cluster to retrieve the data to base the calculation upon. In case of increasing application load, Minddistrict can scale the infrastructure by adding application servers.

**Database cluster**

Minddistrict uses a [ZEO](http://www.zodb.org/documentation/guide/zeo.html) cluster to store the application data. The cluster consists of multiple nodes, in order to be able to fail-over.

The data of each Minddistrict customer is stored separately in the object database; it is not possible to access the data of customer A’s from the application for customer B.

**Static resource servers**

Static resources (video, audio, javascript, CSS and images) are served by servers dedicated to this task. This leads to faster load times of web pages.

**Load balancing**

The load balancer unwraps SSL traffic and routes the traffic to the proper application or static resources server.

**Backups**

Application data is back-upped on an hourly basis. Every night, a full backup is transfered to an off-site backup server. Every three months, an encrypted backup of these three months is transferred to the vault of a notary.

**Application security**

The Minddistrict application is built using [Zope](http://zope.org/) technology. Zope is a framework for building secure web applications, which has been used for more than 10 years and has an outstanding security record.

All information is transferred over SSL connections.

Email is an insecure medium. The Minddistrict application sends emails, but these never contain confidential information. The emails are pointers to the actual message, which lives in the application and is accessible after logging in with a password.

It is not possible to fish for usernames using the lost-password functionality.

**Server security**

In order to provide proper server security, the following best practices are followed:

Minddistrict administrators have SSH access to the production machines. The user accounts don’t have passwords, SSH-key-based login only. The servers are only accessible over a VPN connection.

Root passwords are stored in a file shared between administrators, encrypted using PGP technology.

Operating system software updates are first tested on testing machines, before being rolled out to staging and production environment. The Administrators subscribe to different security bulletins in order to keep up-to-date on security threats.

**Privacy**

Only certain Minddistrict employees are authorized to access the production servers.

Software bugs are never fixed using hotfixes in the production environment. The production database is downloaded to a testing machine, the data is anonymized before bug hunting. After the bug has been fixed, a new release is made an deployed.

**Monitoring**

The health and performance of the Minddistrict servers and applications are monitored using [Nagios](http://nagios.org/) technology on internal servers and externally through [pingdom](http://pingdom.com/).

[Munin](http://munin.org/) is used to collect historic information, based on which Minddistrict Operations can make informed decisions on how to scale the infrastructure.

## Use of co-intervention (if applicable)

## Not applicable to this study

## *.* INVESTIGATIONAL PRODUCT

Not applicable to this study

# NON-INVESTIGATIONAL PRODUCT

Not applicable to this study.

# METHODS

## Study parameters/endpoints

The health-economic analyses combine clinical outcomes with cost estimates. Measures of these primary variables are described in this section.

### Main study parameter/endpoint

#### Clinical outcomes

Primary clinical outcomes are 1) severity of anxiety symptoms measured with the Beck Anxiety Inventory (BAI), 2) quality-adjusted life years (QALY’s), derived from the Euro Quality of Life questionnaire (EQ-5D-3L) and health-related quality of life, tapped by the SF-36 Health Survey.

### The Beck Anxiety Inventory (BAI) (Beck et al., 1988)consists of twenty-one questions about how the subject has been feeling in the last week, expressed as common symptoms of anxiety (such as numbness and tingling, sweating not due to heat, and fear of the worst happening). It is designed for an age range of 17–80 years old. Each question has the same set of four possible answer choices, which are arranged in columns and are answered by marking the appropriate one with a cross. The BAI has a maximum score of 63. For this study, treatment response is defined as a symptom reduction of the baseline BAI symptom severity score of at least 30% and remission a score reduction of at least 30% reduction plus a total score <11.

**The EQ-5D-3L** (EuroQol, 1990; Lamers, 2005) will be administered at every assessment moment (T0-T3) to assess *general well-being*. The questionnaire consists of five questions that tap mobility, self-care, daily activities, pain and mood. Each item has three response categories, ranging from 0 (*no problems*) to 3 (*severe problems*). In addition to this, participants use a VAS scale to rate their health on a scale ranging from 0 (*worst possible health*) to 100 (*best possible health*). The answers on the five questions are combined in a number sequence that corresponds with the five answers, for example 03210. The total number of possible sequences is 3^5^=243. Each sequence stands for a certain health state. On these health states, a value (utility) has been placed (Lamers et al., 2006), which in turn is used to determine the quality-adjusted life years (QALYs). This is done by calculating the QALYs gained between the follow-up periods by weighing the length of time spent in a particular health condition by the utility score (Drummond, 2005).

### The Short Form Health Survey (SF-36) will be used to assess *health-related quality of life* (Aaronson et al., 1998; Bech et al., 2003; Ware, 2000). This questionnaire consists of 36 questions that are scored on a 8 multi-item scales, which assess physical functioning, role limitations caused by physical health problems, bodily pain, general health perceptions, vitality, social functioning, role limitations caused by emotional problems and general mental health. The raw scores are converted to a scale ranging from 0 to 100 with higher scores being indicative of better levels of functioning. SF-36 scores will provide a second source to determine QALYS, through the application of the Brazier algorithm (Brazier et al., 2002).

Secondary study parameters/endpoints (if applicable).

**Cost outcomes**
Cost estimates include 1) the costs of offering the treatments and 2) Patients’ out-of-pocket costs (non-medical), such as the costs of travelling to the health services and the patients’ time costs of travelling, waiting and receiving treatment, which are determined with the standard cost prices as listed in the pertinent Dutch guideline for economic evaluation (Tan et al., 2012). Furthermore, 3) Costs stemming from health care uptake, including costs of medication, and 4) Costs stemming from productivity losses due to absenteeism and lesser efficiency while at work (presenteeism) are assessed with *The Trimbos/iMTA questionnaire for Costs associated with Psychiatric Illness* (TiC-P; Hakkaart – van Roijen et al., 2002.

### TiC-P is the most widely used health service receipt interview for economic evaluations in the Netherlands. The TiC-P consists of 46 questions, divided over two parts. Part 1 entails the health care uptake at relevant health care providers in the past 4 weeks, such as medication intake, and the number of contacts within the mental health care setting, with the GP and with other medical specialists. To determine the costs associated with these contacts, the care consumption is multiplied by the cost price described in the before mentioned guideline. Part 2 of the TiC-P entails loss of productivity in the past 4 weeks. This is measured by enquiring about the number of days absent from work and the number of days with reduced efficiency due to feeling ill. The costs of productivity losses will be based on the gender and age specific friction costs, as outlined in the Dutch guideline for costing (Hakkaart van Roijen L, 2010).

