**CEA/CUA**

Costs will be assessed at pre-, mid-, post-treatment and at one-year follow up. As the TIC-P cost date covers a period of three months, all costs will be extrapolated to a 12 months period assuming a stability of costs during the time frame. T-tests will test the change for each cost domain. As cost data will not be normally distributed, p-values will be estimated using a multilevel model (with repeated measurements to control for dependency between the measurements) after which a bootstrap analysis on the parameters is performed (10,000 replications, to generate a reliable cost estimate [23]. An incremental cost-effectiveness ratio (costs per case response or remission) and will be calculated (ICER =(mean costs blended eHealth treatment-mean costs TAU)/(mean bCBT -mean CBT-TAU). The mean costs, including all medical and non medical costs, of the patients in the blended eHealth condition will be subtracted from the mean costs of the patients in the TAU condition. This difference will be then be divided with the subtracted effects (case of response or remission on the BAI). This procedure will be bootstrapped 10,000 times, generating an estimation of the blended eHealth treatment groups’ incremental costs in relation to their incremental health benefit. Additionally an incremental cost-utility ratio (costs per QALY) will be calculated; this procedure is identical to the cost-effectiveness ratio with the exception that instead of a case of response or remission, an additional quality adjusted life year is calculated (QALY). Finally, to test the robustness of the results, we will conduct a sensitivity analyses, to investigate how sensitive the ICERs will be to changes of cost estimates (for example difference in costs per iCBT contact, type of psychologists and number of sessions). For decision-making purposes, the ICER acceptability curve will be plotted for various willingness-to-pay (WTP) ceilings, which helps making judgments about whether the blended intervention offers good value for money, relative to treatment as usual. One-way sensitivity analyses directed at uncertainty in the main cost drivers will be performed to gauge the robustness of our findings across a range of likely values of those parameters.

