**BIA**

To assess how health care budgets are changed by offering blended CBT for depression compared to CBT as usual, a *budget impact analysis* (BIA) will be conducted as outlined in Mauskopf et al. (2007). The BIA will include 1) the perspective of the public purse (in Dutch: Budgettair Kader Zorg), and 2) the perspective of the health care insurer and health care service provider. For each perspective, we consider costs when 10%, 20%, 30% and 100% of the target group receive bCBT. These scenarios will be compared with the base-case scenario, reflecting current care, where 0% of the target group is offered bCBT. When taking the societal perspective, we will consider the costs of offering the health care interventions (also the interventions offered in routine medical care for this particular target group), patients’ out of pocket costs, and costs stemming from productivity losses. Treatment costs will be based on the full economic cost prices (standard cost prices as reports in the Dutch Costing Manual). Productivity losses will be valued using the average gender and age specific productivity levels in the Dutch working population. When taking the perspectives of the public purse (BKZ) and the health insurance companies’ perspective, the focus will be restricted solely to the direct medical costs. For this, the average tariffs of the Dutch Health Authority will be used (NZa). The Budget Impact Analysis (BIA) will be conducted using a health economic (Markov cohort) simulation model.

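### Productivity loss is labelled friction cost, but the linear extrapolation to 12 months has no exception for absenteeism, so long absences can be charged beyond the friction period

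*Protocol*

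**What the plan says.** Section 8.1.2 (cost outcomes, TiC-P paragraph) sets the valuation: "The costs of productivity losses will be based on the gender and age specific friction costs", with a reference to the Dutch costing guideline. It also sets the measurement: "Part 2 of the TiC-P entails loss of productivity in the past 4 weeks", and "This is measured by enquiring about the number of days absent from work", together with days of reduced efficiency. The paragraph mentions no item on when an absence began, and the protocol nowhere states the length of the friction period.

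Section 10.1 (CEA/CUA) takes cost data at four time points: "Costs will be assessed at pre-, mid-, post-treatment and at one-year follow up". It then gives the scaling rule: "As the TIC-P cost date covers a period of three months, all costs will be extrapolated to a 12 months period". The rule rests on an explicit premise that costs do not change over that year. Productivity losses are not exempted, and the recall window is now three months instead of 4 weeks.

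The BIA paragraph of section 10.1, where it describes the societal perspective, uses another wording: "Productivity losses will be valued using the average gender and age specific productivity levels in the Dutch working population". It mentions no friction limit.

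**The concern.** Friction costing is limited in time: an absence costs production until the worker is replaced, and nothing after that. An assumption that costs stay stable over 12 months is the opposite of this for a continuing absence. If the scaling rule is applied as written, the limit that distinguishes friction costs from full-absence (human-capital) costs may not survive it.

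Productivity loss is one of the four cost components in section 8.1.2 and enters the numerator of both the cost-effectiveness and the cost-utility ratio under the societal perspective. It need not be small: section 1 puts absenteeism in anxiety disorders at EUR 998 million a year, against EUR 286 million of healthcare costs. A few long-term absentees charged for a whole year would put a heavy tail on each arm's mean cost. The point concerns absence only; days of reduced efficiency at work are a separate item.

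**Working it through.** The protocol states no figure for productivity cost, so there is none to reproduce. The check follows one patient, absent throughout the recall window, through the stated rules.

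**Inputs from the protocol.** Recall window w = 4 weeks (section 8.1.2) or three months, taken as 13 weeks (section 10.1). Target period 12 months = 52 weeks (section 10.1). For scale only: 78 patients per arm (section 3), and an expected cost difference of 832 and a cost standard deviation of 800 (section 4.4).

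**Assumptions, not in the protocol.** Friction period F, varied. Production value EUR 1,000 per week.

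**Formulas.**
- Limit applied inside the window, then scaled: weeks charged = min(w, F) × 52/w.
- Scaled first, then limited as one continuous spell: weeks charged = min(52, F).

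**Weeks charged.**

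| F (weeks, assumed) | w = 4, limit then scale | w = 13, limit then scale | Scale then limit |
|---|---|---|---|
| 4 | 52 | 16 | 4 |
| 8 | 52 | 32 | 8 |
| 10 | 52 | 40 | 10 |
| 13 | 52 | 52 | 13 |
| 16 | 52 | 52 | 16 |
| 26 | 52 | 52 | 26 |
| 52 | 52 | 52 | 52 |

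With the 4-week window the charge is 4 × 13 = 52 weeks for any F of 4 weeks or more. With the three-month window it is 13 × 4 = 52 weeks for any F of 13 weeks or more. Below those values the limit does act inside the window, but scaling carries the charge back above F: F = 8 with w = 13 gives 8 × 4 = 32 weeks, and F = 2 with w = 4 gives 2 × 13 = 26 weeks. Only a limit applied after scaling holds the charge at F.

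**Illustration of scale.** Excess weeks for one full-year absentee, times EUR 1,000, divided by 78:
- w = 4, F = 10: (52 − 10) × 1,000 / 78 = EUR 538.
- w = 13, F = 10: (40 − 10) × 1,000 / 78 = EUR 385.
- w = 13, F = 13: (52 − 13) × 1,000 / 78 = EUR 500, the largest value for this window.
- Either window, F = 26: (52 − 26) × 1,000 / 78 = EUR 333.

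Over F = 10 to 26 weeks the shift in an arm mean is EUR 333 to 538 (4-week window) or EUR 333 to 500 (three-month window). Against 832, that is 40% to 65% or 40% to 60%.

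**Effect on spread.** One excess value x among 78, with the other 77 at zero excess, has a standard deviation of x/√78. For x = 26,000 this is about EUR 2,900, and for x = 42,000 about EUR 4,800. Section 4.4 plans for 800.

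**The case against.** The strongest reply is that section 8.1.2 adopts friction costing as the cited guideline sets it out, and that method includes its time limit. Section 10.1 does not say whether the limit comes before or after annualising. Applied afterwards, it binds for every friction period below 52 weeks and the excess disappears. The order of steps could be left to an analysis plan. This stands against one tempting inference, that the friction limit can never bind: the documents do not say so. It does not clear the text, because the stated rule extends to every cost, assumes stability and exempts nothing. An analyst who follows it literally defeats the method named in section 8.1.2.

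A reader might also take the 40% to 65% as an estimate of bias, or infer that one or two patients will decide the sign of the ratio. Neither is supported. The figures rest on an assumed friction period and weekly value, on one absentee with no counterpart in the other arm, and, at the upper end, on the 4-week window when the extrapolation sentence itself uses three months. Absence already running at baseline precedes randomisation and is balanced in expectation, so it adds noise and no systematic shift.

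A full-year charge also requires that a single window be annualised. The protocol does not say how the four assessments are combined, so nothing firm can be said about a period-by-period sum.

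There is partial mitigation. Section 2 also names a healthcare perspective, which would leave productivity loss out. Section 10.1 plans one-way sensitivity analyses on the main cost drivers, and productivity might qualify, although the examples given there are cost per contact, type of psychologist and number of sessions.

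**Conclusion.** The concern holds as a conflict between a stated method and a stated rule. Time-limited friction valuation and linear scaling of every cost on a stability assumption cannot both be followed for a long absence. Taken literally, the rule charges a patient absent throughout the window 52 weeks if the friction period is at least as long as the window, and more than the friction period if it is shorter.

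The effect on the trial's result cannot be computed, because the protocol gives no friction period, wage price or absence rate. The euro figures above show only that one record could be large relative to the planned cost difference and the planned standard deviation. The expected harm is mainly extra variance in the societal cost difference; a bias towards either arm is not shown. Two textual conflicts add to the ambiguity and are firm in themselves: 4 weeks against three months for the recall window, and friction costs against average productivity levels for the valuation. This should be settled before costs are analysed.

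**What to change.** In section 10.1, exempt absenteeism from uncapped linear extrapolation. State the friction period taken from the guideline cited in section 8.1.2, and state that the limit is applied after annualising, so that a patient's annualised continuous absence cannot exceed it.

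If the form records when an absence began, apply the limit per spell and count time already elapsed before baseline. If it does not, limit each patient's total annualised absence and say that this is an approximation that may under-count several separate spells. Spells should not be rebuilt from consecutive assessments: T2 and T3 lie 52 weeks apart, and absence at both does not establish one continuous absence.

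Report uncapped valuation as a sensitivity analysis. Reconcile the recall window between sections 8.1.2 and 10.1, since it sets the scaling factor (13 or 4), and reconcile the valuation basis between section 8.1.2 and the BIA paragraph.

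The cost is one costing rule, two wording corrections and one further analysis run. The version that limits total absence needs no new data; its price is the under-counting just described.
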